### Blinding

A double-blind design was adopted in this study. Investigational drugs are XLJDOD compound granule and XLJDOD mimetic agent, which are produced, packaged and provided by Tianjiang Pharmaceutical Group Co. Ltd., Wuxi, China. Mimetic agent is indistinguishable from XLJDOD compound granule in shape, size, taste, color, package, and Lot number. Each medication bag will be labelled with a unique identity number, which corresponds to the random number obtained by IWRS. Researchers, participants, statisticians, and data administrators will be blind to the treatment allocation plans throughout the trial in order to reduce the bias to the greatest extent.

### Data collection and monitoring

All participant data will be recorded on the written case report forms (CRFs), and then dual-input into and managed in form of an electronic case report form (eCRF) through an Electronic Data Capture (EDC) system. Each trail site should designate a person who is strictly trained to be responsible for the preliminary examination of the CRFs and inputting the data into eCRFs. Participants will be contacted periodically to obtain follow-up data. The EDC system will check the data automatically and data managers will review the eCRFs regularly. Suspicious data will be filled in the query list and answered by investigators. In this study, monitors with medical background will ensure the progress of trial is conducted, recorded, and reported in accordance with the protocol, and Standard Operating Procedures (SOPs). The number of site visits should meet the needs of clinical research quality control. After each site visit and/or other trial-related communication, a written report from the monitor to the sponsor is requisite.

### Sample size calculation

The primary Outcome of this study is the rate of 2-year DFS in stage IIIB or IIIC colon cancer. Based on the literature and previous study, it is assumed that the 2-year DFS rate of control group is 0.70 (70%) and of the intervention group is 0.80 (80%). Taking a two-sided significance level of 5% and power of 80% (α = 0.05, β = 0.10), the intervention group and the control group are allocated at a ratio of 1:1. Considering a dropout rate of 20%, the sample size is not less than 364 cases in each group. Therefore, a total sample size of 730 cases is set up in this study (*n* = 365 in each group).

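### The sample-size paragraph pairs 80% power with β = 0.10, which contradict each other; the stated 364 per group matches β = 0.20

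*Protocol article*

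**What the plan says.** The error rates are given in the protocol article under Sample size calculation: "Taking a two-sided significance level of 5% and power of 80% (α = 0.05, β = 0.10". The other inputs are in the same paragraph:

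- Endpoint: "The primary Outcome of this study is the rate of 2-year DFS in stage IIIB or IIIC colon cancer".
- Control group: "it is assumed that the 2-year DFS rate of control group is 0.70 (70" per cent).
- Intervention group: "of the intervention group is 0.80 (80" per cent).
- Allocation: "the intervention group and the control group are allocated at a ratio of 1:1".
- Result: "Considering a dropout rate of 20%, the sample size is not less than 364 cases in each group", which is then set at 365 per group, 730 in total.

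No other section of the article states a power or a β.

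**The concern.** Power and β are complements. A design has 80% power with β = 0.20, or 90% power with β = 0.10, but the sentence asserts one half of each pair. The two readings differ by a factor of two in the planned false-negative risk (20% v 10%), and the sample sizes they require are far apart.

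The figure matters because it is a stated error rate for the primary outcome. Someone who takes up the β and passes over the power could credit the design with a smaller chance of missing a 10-point benefit than it was planned to have. Someone trying to reproduce the calculation cannot tell from the wording alone which value was meant.

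**Working it through.** **Inputs**, all from Sample size calculation: p₁ = 0.70, p₂ = 0.80, two-sided α = 0.05, 1:1 allocation, 20% dropout. Dropout is applied as n/(1 − 0.20).

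**Formula** (two proportions, unpooled variance), evaluable patients per group:

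n = (z₀.₉₇₅ + z₁₋β)² × [p₁(1 − p₁) + p₂(1 − p₂)] / (p₂ − p₁)²

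The variance term is 0.70 × 0.30 + 0.80 × 0.20 = 0.21 + 0.16 = 0.37. Divided by 0.10² = 0.01, this gives 37.

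**Reproducing the stated figure, β = 0.20**

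- (1.960 + 0.842)² = 7.849 with unrounded quantiles.
- 7.849 × 37 = 290.4, so 291 evaluable per group.
- 291/0.8 = 363.75, so 364 per group. This is the stated number exactly.

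**The same calculation at β = 0.10**

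- (1.960 + 1.282)² × 37 = 388.8, so 389 evaluable per group.
- 389/0.8 = 486.25, so 487 per group, or 974 in total.

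**Does the choice of formula matter?** Per-group numbers after dropout, two-sided 5%. The log-rank rows use HR = ln 0.80/ln 0.70 = 0.626 and count events over a fixed 2 years.

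| Method | β = 0.20 | β = 0.10 |
|---|---|---|
| Unpooled two-proportion | 364 | 487 |
| Arcsine | 365 | 489 |
| Pooled two-proportion | 368 | 490 |
| Log-rank, Schoenfeld | 358 | 480 |
| Log-rank, Freedman | 370 | 498 |

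Every β = 0.20 entry lies within 6 of 364, and every β = 0.10 entry is at least 116 above it. A more favourable log-rank version counts all events over the 2 to 3 years of follow-up implied by 1 year of enrolment, assuming exponential DFS. It still needs 399 to 414 per group at β = 0.10.

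**Power at the planned size.** 365 less 20% is 292 evaluable per group.

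- Unpooled: 0.10/√(0.37/292) − 1.960 = 2.809 − 1.960 = 0.849, which gives 80.2%.
- Pooled: 79.8%.

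Both agree with the 80% given in words.

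**The case against.** The strongest reply is that this is a misprint with no effect on the design. The correct power stands directly before the wrong β, the sample size agrees with that power, and no conduct, analysis or decision rule depends on the printed β. After a null result, the evidence against a 10-point benefit comes mainly from the confidence interval and not from the planned β. All of this stands, and it limits the severity. It does not remove the error: the two values cannot both be true, and no other section says which was intended.

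A second reply is that the primary test is a log-rank test (Statistical analysis section), so actual power may exceed 80%. With 292 evaluable per group, log-rank power is 79% to 81% on 2-year events and about 86% to 87% if all events over 2 to 3 years count (exponential assumption). With all 365 evaluable, two-proportion power is 87.9%. So 80% is a planning figure, conditional on a two-proportion comparison in which dropouts contribute nothing; it is not a settled statement of the trial's power. This does not rescue β = 0.10. In these calculations power passes 90% only for a log-rank test with no dropout and all 2 to 3 years of events, which departs from the section's own 20% dropout and 2-year endpoint.

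A reader might also infer that the trial promised 90% power and is short of it by 244 to 250 patients (974 or 980 less 730). The documents do not support that. Ninety per cent power is never stated, and the only power given, 80%, is the one the sample size meets. The larger totals serve only to show that β = 0.10 was not the value used.

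**Conclusion.** Wrong as written. The printed type II error, 0.10, is half the 0.20 on which the sample size was built. The 80% power, 364 per group and total of 730 are consistent with one another. The contradiction follows from the definition of power and needs no assumption. The conclusion that 0.20 was the working value rests on the stated rates, two-sided 5%, 1:1 allocation and dropout applied by dividing by 0.8. The exact match to 364 is with the unpooled two-proportion formula, but the other formulas tried point the same way. Severity is low to moderate: it is a stated error rate for the primary outcome, but one figure corrects it.

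**What to change.** Restate the error rates as: two-sided α = 0.05, power 80% (β = 0.20). Leave the sample size at 730. The sponsor should confirm that 80% was the intended power, as the calculation indicates.

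The cost is one corrected number in the protocol, with no additional patients. The analysis plan is not available, so nothing shows that it repeats the error; whoever writes it should carry forward the corrected value. Naming the formula or adding a target number of events would be optional detail and is not part of this correction.

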### Statistical analysis

#### Selection of statistical analysis data set

##### Full Analysis Set (FAS)

It refers to the modified subject set that is as close as possible to the principle of Intention-to-treat (ITT) analysis (primary analysis should include all randomized subjects). The data set is obtained after all randomized subjects are eliminated by the minimum and reasonable method.

##### Per-protocol Set (PPS)

PPS comprises subjects who complete the 6 courses of treatment without serious protocol violations. Meanwhile, the baseline variables of the subjects are complete, and primary variables can be measured.

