### Intervention measures

#### Intervention group

Subjects in the intervention group will be treated with XLJDOD compound granule. Treatment will begin within 3 months after standard adjuvant chemotherapy and compliance will be continuously monitored. XLJDOD will be taken twice a day, infused with warm water, 1 h after lunch and dinner. One course of treatment will take 28 days in 1 month, and 2- to 3-day rest. Treatment will continue for 6 courses.

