### Study procedure

The duration of this study will be 3 years, with 1 year of enrollment and a minimum follow-up period of 2 years. The specific measurements and time points for data collection of this study are outlined in Fig. 2, which must be followed as accurately as possible. Treatment will be started within 7 days of the randomization and last for 6 months. Eligible patients will be followed up every 3 months until death or the end of this study. The researcher should obtain written informed consent before conducting study-specific procedures for patients enrolled in the trial.

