### Outcomes

#### Primary outcome

Two-year disease-free survival (DFS) rate: DFS is defined as the time from the date of randomization to the date of disease recurrence, second primary cancer (colon cancer or other cancer), or death from any cause, whichever occurred first. 2-year DFS rate is defined as the percentage of patients alive without disease recurrence at 2 years measured from the randomization date. Disease recurrence includes any condition of the following—unequivocal radiological evidence of colon cancer locoregional recurrence or distant metastases, positive histology or cytology (e.g. peritoneal or pleural cytology), colonoscopic evidence of locoregional cancer recurrence at the anastomotic site and its adjacent areas.

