##### Safety set (SS)

SS is defined as the data set composed of all subjects who receive at least one dose of XLJDOD compound granule after randomization.

In this study, the FAS data set is the primary analysis set. In addition, a per-protocol analysis will also be performed as a sensitivity analysis.

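### The per-protocol set requires completion of all 6 courses, so it drops on-treatment deaths and any recurrence that ends treatment, and the sensitivity analysis is selected partly on the primary outcome

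*Protocol article*

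**What the plan says.** The section Per-protocol Set (PPS) defines the set by completion: "PPS comprises subjects who complete the 6 courses of treatment without serious protocol violations". It then adds further conditions: "Meanwhile, the baseline variables of the subjects are complete, and primary variables can be measured". It makes no exception for a patient whose treatment ended because a DFS event occurred.

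Two other sections place that condition in time. Study procedure says "Treatment will be started within 7 days of the randomization and last for 6 months", and Intervention group says "Treatment will continue for 6 courses", with one course per month. Under Primary outcome, "DFS is defined as the time from the date of randomization to the date of disease recurrence", with second primary cancer and death from any cause also counting as events.

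The roles of the sets are given at the end of Safety set (SS): "In this study, the FAS data set is the primary analysis set", and "a per-protocol analysis will also be performed as a sensitivity analysis".

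**The concern.** Membership of the set is decided about 6 months after time zero, by something that the primary outcome can itself prevent. A patient who takes every scheduled dose and dies in month 4 has followed the protocol perfectly and still cannot be in the set. The same holds for a compliant patient who stops in month 4 because of a recurrence or a second primary cancer. These are primary-endpoint events, and they are lost for reasons unrelated to adherence.

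A per-protocol analysis is meant to show whether the FAS result holds among adherent patients. It is the only stated efficacy analysis on a different population; the other sensitivity analysis, the Cox model, changes the covariates. If the set is thinned of early events, agreement or disagreement with the FAS is hard to interpret. Drug is given only in months 0–6, which is the period in which this set sees least.

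**Working it through.** **Inputs.** 2-year DFS of 0.70 (control) and 0.80 (intervention), and 365 patients per arm, from Sample size calculation. Treatment of 6 months, from Study procedure. The article gives no 6-month DFS and no hazard shape, so these are assumed and varied. Counts use all 365 per arm, with no allowance for dropout.

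**The plan's own figure.** With unpooled variance, two-sided 5% and 80% power:

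n = (1.960 + 0.842)² × (0.70×0.30 + 0.80×0.20) / 0.10² = 7.85 × 0.37 / 0.01, which rounds up to 291 per arm; 291 / 0.80 = 364.

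This matches the stated minimum, so 0.70 and 0.80 are the right inputs for what follows.

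**Constant hazard, every month 0–6 event removed.** S(6) = S(24)^0.25, and apparent 2-year DFS among those left = S(24)/S(6).

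- Control: S(6) = 0.70^0.25 = 0.9147. Events by 6 months are 8.5%, or 31.1 of 365. Apparent 2-year DFS = 0.70/0.9147 = 76.5%.
- Intervention: S(6) = 0.80^0.25 = 0.9457. Events by 6 months are 5.4%, or 19.8 of 365. Apparent 2-year DFS = 0.80/0.9457 = 84.6%.
- Expected 2-year events: 365×0.30 + 365×0.20 = 109.5 + 73 = 182.5. Share removed: (31.1 + 19.8)/182.5 = 28%.
- Difference: 8.1 points instead of 10.0.
- Hazard ratio before removal: ln 0.80 / ln 0.70 = 0.63. After removal: ln 0.846 / ln 0.765 = 0.63, unchanged.

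**Constant hazard, only month 0–3 events removed.** This fits a case in which later recurrences are found at the month-6 visit, when the courses are complete or nearly so.

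- Control: 1 − 0.70^0.125 = 4.4% (16 patients); apparent 2-year DFS = 0.70/0.9564 = 73.2%.
- Intervention: 1 − 0.80^0.125 = 2.8% (10 patients); apparent 2-year DFS = 0.80/0.9725 = 82.3%.
- Share removed: 26/182.5 = 14%. Difference: 9.1 points.

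**Ranges.**

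- Only 25% to 75% of patients with a month 0–6 event removed, constant hazard: difference 9.6 to 8.6 points.
- Full removal with Weibull shape k, S(6) = S(24)^(0.25^k), k from 0.75 to 1.5: 40% down to 14% of 2-year events removed, difference 7.2 to 9.1 points.

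**Effects confined to, or different in, the treatment period.** Control hazard λ = −ln 0.70 / 2 = 0.178 per year, full removal:

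- HR 0.5 in months 0–6, then 1.0. All randomized: 73.2% − 70.0% = 3.2 points. Per-protocol set: 76.5% − 76.5% = 0.
- HR 1.5 in months 0–6, then 0.63. All randomized: 74.0% − 70.0% = 4.0 points. Per-protocol set: 84.6% − 76.5% = 8.1 points.

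In the first case a benefit during treatment disappears. In the second an early harm disappears and the apparent benefit doubles.

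**The case against.** **Exclusion at recurrence is not stated.** A reader might infer that every patient who relapses in the first 6 months leaves the set, so that its members have a guaranteed event-free half-year. The article does not support that. Recurrence is not among the Withdrawal criteria, and no section says that study treatment stops when it is found. A patient could recur, finish the 6 courses and remain in the set with the event counted. Only survival to the end of treatment is guaranteed. This part of the objection stands, and it makes the full-removal figures a maximum for a given hazard shape.

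**The planned test need not be biased.** The comparison is by log-rank, with Cox regression in support. Under proportional hazards with all early events removed, the hazard ratio stays at 0.63; the analysis loses events and precision, and a smaller difference is conservative for a superiority claim. The same rule also applies to both blinded arms. This stands for that scenario. It does not cover effects that differ between the treatment period and later, nor the inflation of absolute DFS.

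**The main conclusion is safe.** The FAS is primary and keeps early events. This stands fully and limits how much the point matters.

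**The SAP will settle it.** A separate SAP is planned, and an article condenses. But the completion rule is a stated definition, not a gap. An SAP that follows it as written carries the selection forward.

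**Conclusion.** The point holds for the supportive analysis only. The completion rule lies inside the DFS window, so on-treatment deaths are excluded with certainty, and recurrences or second primaries are excluded whenever they end treatment. The per-protocol result is therefore selected partly on the outcome, overstates DFS in both arms and can mask what happens during treatment. The direction of any distortion in the treatment comparison is not fixed.

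Its size cannot be read from the article. On the plan's 70% and 80%, the scenarios above remove between 14% and 40% of 2-year events when all month 0–6 events are taken out, and the 10.0-point difference becomes 7.2 to 9.1 points. Partial removal under a constant hazard brings it closer to 10.0. The constant-hazard figures of 28% and 8.1 points describe maximum removal and should not be read as a forecast. Nor do they imply that the FAS result or the hazard ratio under proportional hazards is compromised. The change is worth making, but it is not critical to the trial's primary conclusion.

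**What to change.** Define per-protocol compliance over the period from randomization to the earlier of the first DFS event and the end of the 6 courses. Include patients whose intake of the doses scheduled before that date falls within the 80–120% range already used in Withdrawal criteria, who have no serious protocol violation, and who meet the existing data conditions. A compliant patient with a recurrence, second primary cancer or death on treatment then stays in the set with the event counted. Write this into the SAP, and align the protocol definition with it, before unblinding.

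If an analysis of completers is still wanted, present it separately as a 6-month landmark analysis and label it so.

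The cost is a small amount of extra work to derive the set, since intake must be computed up to a patient-specific date. Intervention group already provides for continuous monitoring of compliance, so no new data are needed. Sample size, treatment and the primary analysis do not change.

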##### Safety set (SS)

SS is defined as the data set composed of all subjects who receive at least one dose of XLJDOD compound granule after randomization.

In this study, the FAS data set is the primary analysis set. In addition, a per-protocol analysis will also be performed as a sensitivity analysis.

#### Content and method of statistical analysis

The statistical analysis plan will be developed by an independent statistician who does not participate in the study in consultation with the principal researchers. SAS 9.4 will be employed for statistical analysis. The content will cover actual number of subjects enrolled in both groups, shedding and exclusion of cases, demographics and other baseline characteristics, compliance, efficacy analysis, and safety analysis.

The description of qualitative data will use frequency table, percentage or proportion. Quantitative data will be expressed by mean, standard deviation, median (P25, P75) and minimum/maximum values.

The Log-rank test will be used as the primary analysis for comparison of 2-year DFS rate in two groups, and the Cox regression will be used to adjust for covariates (such as study centers) as sensitivity analysis. Pre-determined subgroup analysis factors include sex, age (< 65 yr versus ≥ 65 yr), tumor location (left colon versus right colon), tumor pathological stage (IIIB versus IIIC), T classification (T1, T2, or T3 versus T4), N classification (N1 versus N2), the presence or absence of venous invasion. The comparison of 1,2-year RR and median OS will be performed by Log-rank test. The QoL score at different time points will be analyzed using mixed effect model and adjusting for study centers. Safety outcomes will be evaluated by summarizing the number of abnormal subjects and comparing the rate between groups. All data statistics will be analyzed by using a two-sided test, and the test statistics and their corresponding *p*-values will be given, with a significance level setting at *p* < 0.05.

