## Introduction

According to estimates from the International Agency for Research on Cancer (IARC), colorectal cancer has the third highest incidence and the second highest mortality worldwide in 2020, in which the occurrence and death risk of colon cancer is about half higher than that of rectal cancer. The prevention and control situation is still grim with about 1.15 million new cases and about 0.58 million deaths due to colon cancer in 2020 [1]. For those without evidence of metastatic disease, surgical resection is the main treatment modality, and it is commonly followed by adjuvant chemotherapy, which can bring survival benefits for patients with colon cancer [2, 3]. Unfortunately, approximately 1/3 of patients have stage III disease at diagnosis because of lymph node involvement [4–6], around 40% of them relapse even after surgery and adjuvant chemotherapy [7, 8].

The main cause of death after radical resection for colon cancer is tumor recurrence [9]. The study found that the risk of recurrence is highest in the first 2 years and that the risk of death peaks about 2 years after treatment [10]. Stage III colon cancer comprises a highly heterogeneous group of patients, with a 2-year rate of disease-free survival (DFS) of about 91% (IIIA), 79% (IIIB) and 60% (IIIC), respectively [11]. In addition, high levels of symptom burden-fatigue, insomnia, distress, constipation, and diarrhoea-is often expected shortly after treatment, which can result in significant limitations in daily activities and overall impairment in health-related quality of life (QoL) [12]. However, there lacks a recognized and effective therapeutic strategy in modern medicine to prevent recurrence after radical resection and chemotherapy for patients with stage IIIB or IIIC colon cancer. Additional strategies are required urgently in consequence.

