## Methods and design

### Study design

This study is designed as a multicentre, randomized, double-blind, parallel-arm, placebo-controlled trial. Participants will be recruited from following 13 centers, including Sun Yat-sen University Cancer Center, Cancer Hospital Chinese Academy of Medical Sciences, Fudan University Shanghai Cancer Center, West China Hospital of Sichuan University, Jiangsu Province Hospital, Zhejiang Cancer Hospital, Jiangsu Province Hospital of Chinese Medicine, LongHua Hospital Shanghai University of Traditional Chinese Medicine, The First Affiliated Hospital of Guangzhou University of Chinese Medicine, Jiangsu Province Hospital on Integration of Chinese and Western Medicine, The First Affiliated Hospital of Guizhou University of Traditional Chinese Medicine, The First Affiliated Hospital of Soochow University, and The First People’s Hospital of Changzhou. Recruitment performs simultaneously in out-patient clinics and wards. This trial was registered with ClinicalTrials.gov (NCT05709249). This protocol has been developed in accordance with the Standard Protocol Items: Recommendations for Interventional Trials (SPIRIT) [31], and the new extension of the Consolidated Standards of Reporting Trials (CONSORT) for CHM [32] to ensure appropriate high-quality methodology and strict quality control. The clinical study will be conducted for 36 months, from December, 2022 to December, 2025. The flow diagram of this study is depicted in Fig. 1.

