### Randomization and allocation concealment

In this trial, an online centralized randomization system called Interactive Web Response System (IWRS) will perform the block randomization with a 1:1 ratio, permutation block with variable sizes of four, six, eight, or twelve, stratified by the study center. After informed consent, the investigators will log into IWRS to acquire a unique identification code and random number of each participant for participant identification and treatment assignment. IWRS will ensure the allocation concealment. It will only offer a random number to the investigator, and none of the investigators, participants, and outcome evaluators will know from random numbers whether they represent the intervention group or the control group. In case of SAEs that may be associated with experimental drugs, including death, allergic reactions, intolerable severe gastrointestinal reactions, liver and kidney insufficiency, etc., the allocated intervention of participant could be revealed by investigator in the IWRS.

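### The primary log-rank test names neither the randomisation stratum (centre) nor stage IIIB/IIIC; it is valid, but forgoes a small and easily obtained gain in precision

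*Protocol article*

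**What the plan says.** All references are to the protocol article.

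- **Randomization and allocation concealment:** allocation is 1:1 by "permutation block with variable sizes of four, six, eight, or twelve, stratified by the study center". No other stratification factor is given. Under Study design, "Participants will be recruited from following 13 centers".
- **Content and method of statistical analysis, primary test:** "The Log-rank test will be used as the primary analysis for comparison of 2-year DFS rate in two groups". No stratum is attached to it. Covariate adjustment comes second: "the Cox regression will be used to adjust for covariates (such as study centers) as sensitivity analysis".
- **Same section, quality of life:** "The QoL score at different time points will be analyzed using mixed effect model and adjusting for study centers". Centre is therefore in the model for a secondary outcome but not in the primary test.
- **Same section, subgroups:** stage IIIB versus IIIC is one of seven pre-specified subgroup factors. It has no other role in the analysis and is not named among the Cox covariates, although that list is open-ended.
- **Introduction:** stage III disease is described as heterogeneous, "with a 2-year rate of disease-free survival (DFS) of about 91% (IIIA), 79% (IIIB) and 60% (IIIC), respectively". Only IIIB and IIIC are enrolled (Inclusion criteria), so stage is known for every patient before randomisation.

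**The concern.** When randomisation is blocked within centre, the arms are balanced within each centre. If prognosis differs between centres, a test that ignores the blocking uses a null variance that is somewhat too large, so it is conservative and loses some power. The usual remedy is to analyse by the strata used to randomise. Here that is done for quality of life but not for the primary outcome.

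Stage raises a related point. The article's own figures put a 19-point gap in 2-year DFS between the two enrolled stages, nearly twice the 10-point treatment effect in the sample size calculation. Stage is not balanced by design and is not used in the primary test, so any chance imbalance stays in the primary comparison. If a visible imbalance appeared, giving weight to an adjusted result at that stage would look post hoc. The time to settle the question is before unblinding.

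**Working it through.** **Inputs from the article.** Control and active 2-year DFS 0.70 and 0.80, two-sided 5%, 80% power, 20% dropout, 365 per arm (Sample size calculation); IIIB 0.79 and IIIC 0.60 (Introduction); 13 centres (Study design); blocks of 4, 6, 8 or 12 within centre (Randomization).

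**1. The plan's own figure.** With unpooled variance, n = (1.960 + 0.842)² × (0.70×0.30 + 0.80×0.20) / 0.10² = 7.849 × 0.37 / 0.01 = 290.4, so 291 per arm. Then 291 / 0.80 = 363.75, which gives 364. The stated size reproduces at 80% power. Removing 20% from 365 leaves 292 per arm.

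**2. Strength of stage.** Under proportional hazards, HR (IIIC vs IIIB) = ln 0.60 / ln 0.79 = 2.17.

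**3. IIIC share (not stated, so back-calculated).** If 70% is a mixture of 79% and 60%, the share is (0.79 − 0.70) / (0.79 − 0.60) = 0.474. The within-stage treatment HR that then gives 80% in the active arm solves 0.526 × 0.79^h + 0.474 × 0.60^h = 0.80, so h = 0.619.

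**4. Chance stage imbalance.** The SD of the between-arm difference in IIIC share is √(2 × 0.474 × 0.526 / 365) = 3.7 points, with an 18% chance of exceeding 5 points. Two SDs are 7.4 points, and 7.4 × 0.19 = 1.4 points of DFS. Using the 95% range (1.96 SD) and an assumed IIIC share of 30% to 50%, the shift is 1.3 to 1.4 points.

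**5. Power, by simulation.** DFS was exponential with the stage rates above, observed to 2 years, with blocked randomisation in 13 centres. The article gives no between-centre variation, so the SD of the centre log-hazard is assumed. Two setups were used: 292 per arm (6,000 trials per row, 8,000 for SD 0.5), and 730 patients with 20% dropout (4,000 trials). Only comparisons within a row matter.

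| Setup | Centre SD | Unstratified | Centre | Stage | Centre and stage |
|---|---|---|---|---|---|
| 292 per arm | 0 | 81.0% | 80.8% | 81.9% | 80.7% |
| 292 per arm | 0.3 | 80.0% | 80.6% | 81.6% | 81.5% |
| 292 per arm | 0.5 | 80.4% | 81.9% | 81.9% | not run |
| 730, 20% dropout | 0 | 85.1% | not given | 86.4% | 85.4% |
| 730, 20% dropout | 0.3 | 83.6% | 84.1% | not given | 85.3% |

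The simulation standard error of one entry is about 0.5 to 0.6 points. Tests in a row share the same simulated trials, so differences are more precise than that. Against the unstratified test, centre-and-stage stratification ranges from a loss of a fraction of a point to a gain of 1.7 (85.3 − 83.6). If centres do not differ, it gives up 1.0 (86.4 − 85.4) to 1.2 (81.9 − 80.7) points against stage alone.

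**6. Type I error.** At centre SD 0.5, the unstratified test rejects in about 4.1% of null trials and the centre-stratified test in 4.7%. At SD 0.3 no difference is visible beyond simulation error: two runs gave 4.0% and 5.0% unstratified, against 4.1% and 5.2% by centre, and the second setup gave 4.7% to 4.9% for all tests. With no centre effect, the unstratified test gave 5.1%.

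**7. Sparseness.** 13 × 2 = 26 strata. At the planned rates, 584 patients (2 × 292) give about 0.25 × 584 = 146 events, or 146 / 26 = 5.6 per stratum on average, and fewer in small centres.

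**The case against.** The strongest reply is that nothing is broken. The unstratified log-rank is a valid test, its simulated power is at or above the planned 80%, and the required sample size does not change materially. A randomisation p-value already allows for chance imbalance. One SD of stage imbalance moves the difference by 3.7 × 0.19 = 0.7 points, against a standard error of √((0.21 + 0.16) / 365) = 3.2 points, so stage accounts for about (0.7 / 3.2)² = 5% of the variance. All of this stands, and it limits the size of the point.

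The stage figures are also soft. The Introduction gives no time origin for the 79% and 60%, whereas this trial counts DFS from randomisation in patients who are recurrence-free after chemotherapy. The HR of 2.17 may not carry over, and the 47% share is an inference. This stands too. A reader might go further and call stage the strongest prognostic factor the protocol cites. The article does not support that ranking, because the other subgroup factors carry no outcome rates to compare.

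A further reply is that strata are a matter for the analysis plan and that the Cox covariate list is open and could include stage. This is only partly right. The word unstratified is not printed, but the article does assign roles: a plain log-rank as primary and covariate adjustment as sensitivity. Whatever enters the sensitivity model does not change the primary p-value.

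**Conclusion.** The point holds as a modest matter of efficiency and of matching the analysis to the design. The primary test omits the factor used to randomise and the one prognostic factor for which the article gives outcome rates in the enrolled population. The cost is about 0 to 2 power points, slight conservatism if centres differ appreciably, and a DFS shift of about 1.4 points from a 2-SD stage imbalance. These sizes rest on an assumed centre log-hazard SD of 0 to 0.5, a back-calculated IIIC share of 47%, and cited stage rates that hold from randomisation.

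Two stronger readings are tempting and should be resisted. One is that ignoring the randomisation stratum makes the test invalid or inflates false positives. The effect goes the other way, and simulated type I error stayed at about 5% or below. The other is that stratification is free. If centres do not differ, the full set of strata costs about 1 power point against stage alone.

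**What to change.** Amend the analysis section before unblinding so that:

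- the primary test is a log-rank stratified by stage (IIIB/IIIC) and study centre;
- small centres are pooled by a rule based on size alone and fixed before unblinding;
- the hazard ratio comes from a Cox model with the same strata, so that test and estimate match;
- the unstratified log-rank is kept as a sensitivity analysis.

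This changes the primary analysis as the article states it, so it needs a dated amendment and the analysis plan must follow it. Sparse strata lose a little information, which the pooling rule limits. No new data are needed, because centre and stage are recorded for every patient, and randomisation, already under way by centre, is untouched.
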